### Sample size calculation

In determining the appropriate group size in order to demonstrate a significant intervention effect on the primary endpoint, we used Cohen's effect size *d *to determine the difference between the patients' KATZ ADL index scores on the before and after measurement and divided by the SD of the difference scores of the control group as a benchmark for assessing the relative magnitude of ALDS score differences between both strategies. Although an effect size of 0.25 can be defined as small, such a difference in Katz ADL scores may be clinically important.

We have demonstrated that with a total of 506 patients (253 patients per treatment arm) we are able to statistically detect (power 80%, two-sided alpha of 5%) a minimal effect size on the Katz ADL index score. To allow for attrition due to mortality, which is expected to be 25% six months after admission, a total of 674 patients will be included in the trial.

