### Outcomes

#### Primary outcome

The primary outcome measure is the level of ADL functioning six months after discharge from the hospital compared to premorbid functioning two weeks prior to hospital admission. The level of ADL functioning will be measured with the Katz ADL index score [19]. The Katz ADL index score consists of 6 items, with score range from 0 to 6, with a higher score indicating more impairment in ADL. At both time points, the questionnaire will be filled in by the same person (patient or proxy, depending on cognitive impairment)

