### Data analysis

Statistical analyses will be based on an intention-to-treat principle. Baseline assessments and outcome parameters will be summarized using simple descriptive statistics. The main analysis focuses on a comparison between the trial intervention and control group of the primary outcome, the Katz ADL index score. The same approach will be used with regard to the secondary outcome parameters, including survival rates. Survival data will be additionally analyzed using Kaplan-Meier survival curves and the log-rank test.

We will perform a predefined subgroup analysis for discharge destination (patients discharged to home versus nursing home). In all analyses statistical uncertainties will be quantified via corresponding 95% confidence intervals. Separate subgroup analysis will also be conducted on patients at intermediate (ISAR-HP score of two or three) and high risk for functional decline (ISAR-HP score of four or five). Finally, process outcome data will be analyzed qualitatively within the theoretical framework of the adaptive implementation model [23].

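### The trial is powered on six-month survivors, with the expected 25% mortality treated as attrition, yet the analysis is called intention-to-treat without qualification; the survivor comparison can be biased in either direction.

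*Protocol article*

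**What the plan says.** The protocol article defines its endpoint in the Outcomes section as follows: "The primary outcome measure is the level of ADL functioning six months after discharge from the hospital compared to premorbid functioning two weeks prior", the reference point being the admission. It is scored on the Katz index from 0 to 6, higher being worse, and death has no value on that scale.

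The Sample size calculation section bases the design on a small standardised effect ("Although an effect size of 0.25 can be defined as small") and obtains 506 patients, 253 per arm, for 80% power at a two-sided 5% level. It then adds patients for one reason only: "To allow for attrition due to mortality, which is expected to be 25% six months after admission, a total of 674 patients" are planned.

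The Data analysis section opens with "Statistical analyses will be based on an intention-to-treat principle" and makes the main analysis a between-arm comparison of the Katz score. Mortality is a separate secondary outcome, analysed in addition by Kaplan-Meier curves and the log-rank test. Nothing in the article brings deaths into the Katz comparison.

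**The concern.** A patient who dies before six months has no Katz score. Counting such patients as attrition makes the primary comparison one between the survivors of the two arms. Survival happens after randomisation, and a program that follows frail patients through discharge could change it. The survivors of the two arms need not then be alike, and randomisation no longer protects the comparison.

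Two things are at stake:

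- **What is estimated.** An unqualified intention-to-treat label invites the reader to take the Katz result as covering everyone randomised, when about a quarter are expected to be absent from it.
- **Possible bias.** If the program keeps alive patients who then show a worse Katz change, their presence dilutes a real functional benefit. If it raised mortality among such patients, the bias would favour the program.

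**Working it through.** **Inputs from the protocol article.** Two-sided alpha 0.05, power 0.80, effect 0.25 SD, 253 per arm, mortality 25%, 674 enrolled (all Sample size calculation); Katz range 0 to 6 (Primary outcome).

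**Assumed inputs, not in the article.** Intervention-arm mortality m of 20% or 15% against 25% in control; g, the amount in SD by which the Katz change of the extra survivors is worse than that of the other survivors.

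**Step 1: reproduce the evaluable number.** n per arm = 2(1.960 + 0.842)²/0.25² = 2 × 7.85/0.0625 = 251.2, so 252 by the normal approximation. The two-sample t-test gives 252.13, so 253 per arm and 506 in total. Power with 253 per arm is 0.803. The stated figure is reproduced.

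**Step 2: reproduce the enrolled number.** 506/(1 − 0.25) = 674.67, against 674 stated, which is a rounding difference. The alternative 506 × 1.25 = 632.5 does not match. In reverse, 674 × 0.75 = 505.5 survivors, with power 0.802, and 674 × 0.25 = 168.5 expected deaths. The stated power therefore holds when the dead contribute no Katz value.

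**Step 3: size of the possible distortion.** Take 337 randomised per arm and a true effect of 0.25 SD in patients who would survive in either arm. Suppose that the program saves some patients and costs no lives.

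- Share of extra survivors among intervention survivors: f = (0.25 − m)/(1 − m)
- Observed effect: d = 0.25 − f × g
- SE = √[1/(337(1 − m)) + 1/(337 × 0.75)]
- Power = Φ(d/SE − 1.96)

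For m = 0.20: f = 0.05/0.80 = 0.0625. Survivors number 269.6 and 252.75, so about 17 are extra, and SE = 0.0876.

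| Intervention mortality | g (SD) | Observed d | Power |
|---|---|---|---|
| 25% | any | 0.250 | 0.802 |
| 20% | −0.5 (better) | 0.281 | 0.895 |
| 20% | 0 | 0.250 | 0.815 |
| 20% | 0.5 | 0.219 | 0.705 |
| 20% | 1.0 | 0.188 | 0.572 |
| 15% | −0.5 (better) | 0.309 | 0.947 |
| 15% | 0 | 0.250 | 0.826 |
| 15% | 0.5 | 0.191 | 0.601 |
| 15% | 1.0 | 0.132 | 0.335 |

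For m = 0.15, f = 0.10/0.85 = 0.118.

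**Step 4: power of an analysis that keeps everyone.** In simulations of 3,000 trials with 337 per arm, a continuous outcome and a rank test with death as the worst value:

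- Equal mortality of 25%: power 42–43% when death is unrelated to function. A separate simulation, in which frailty drives death and correlates 0.6 with function, gave about 50%.
- 25% v 20%: power 73–86% for g from 1 down to 0, in the first of these simulations.

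**The case against.** **The article never says that the comparison is restricted to survivors.** That is true. The inflation is a recruitment allowance, the analysis section excludes nobody in words, and an unseen analysis plan may say how deaths enter. The survivor reading is an inference from the sample size. It is a firm one, because the scale has no value for death and the stated power fits only about 506 scored patients. A later plan that scored deaths would be a different analysis from the one powered here.

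**Mortality is analysed in its own right.** This also stands: a survival benefit would not be lost, and an imbalance would be visible. But a separate log-rank test does not correct the Katz comparison or tell the reader what it is conditional on.

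**A reader might infer that the plan will understate benefit whenever the program lowers mortality.** The documents do not support that. Lower mortality alone is not enough; the extra survivors must also have a worse Katz change from their premorbid level. The Background section links the same complexity of illness to both death and functional decline, which makes this plausible, but gives no figure. Frail patients with a high premorbid score have less room to worsen on a 0–6 scale. With g = 0 the effect is unchanged, and with g below 0 it is overstated.

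**A reader might also posit extra survivors 1 to 2 SD worse.** In a bivariate normal model with a frailty–function correlation of 0.6, they are only about 0.7 SD worse, so 0.5 to 1 SD is the more defensible illustration.

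**Health care utilization** might seem to share the problem, but the article fixes no specific rule for its analysis that could be faulted.

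**Conclusion.** The point holds in limited form. The sample size is not an arithmetic error. The fault is that it plans a primary comparison conditional on a post-randomisation event while the analysis section claims intention-to-treat without qualification.

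Bias can run either way, most plausibly against the program if it saves patients whose Katz change is worse. With 25% v 20% mortality and extra survivors 0.5 to 1 SD worse, the observed effect falls from 0.25 to between 0.22 and 0.19, and power to between about 70% and 57%. Those inputs are assumptions. Equal mortality with the same kind of patient dying in each arm gives little or no distortion; equal rates alone do not guarantee that the survivors are alike.

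**What to change.** 1. In the Data analysis section, describe the primary Katz analysis as conditional on survival to six months, and qualify the intention-to-treat statement accordingly.
2. Add one prespecified supportive analysis of all randomised patients that ranks death as worse than Katz 6, by an ordinal model or a stratified rank test. Count deaths from randomisation, because randomisation takes place during admission while follow-up outcomes are timed from discharge.
3. Report mortality by arm beside the Katz result.

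The cost is about a paragraph, with no new data or patients. The downside is that the supportive analysis mixes mortality with function and has only about 40–50% power if mortality is equal. It should therefore stay supportive, should not be a condition for claiming benefit, and leaves the sample size at 674. Making it primary would need a new sample size calculation.

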### Data analysis

Statistical analyses will be based on an intention-to-treat principle. Baseline assessments and outcome parameters will be summarized using simple descriptive statistics. The main analysis focuses on a comparison between the trial intervention and control group of the primary outcome, the Katz ADL index score. The same approach will be used with regard to the secondary outcome parameters, including survival rates. Survival data will be additionally analyzed using Kaplan-Meier survival curves and the log-rank test.

We will perform a predefined subgroup analysis for discharge destination (patients discharged to home versus nursing home). In all analyses statistical uncertainties will be quantified via corresponding 95% confidence intervals. Separate subgroup analysis will also be conducted on patients at intermediate (ISAR-HP score of two or three) and high risk for functional decline (ISAR-HP score of four or five). Finally, process outcome data will be analyzed qualitatively within the theoretical framework of the adaptive implementation model [23].

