### Randomisation and blinding

After obtaining informed consent and baseline assessments, patients will be randomised into the intervention or control group (figure 1). The randomisation procedure will be website-based, using permuted blocks and stratified by study centre and level of cognitive functioning (Mini-Mental State examination of ≥ 24 versus MMSE scores of < 24).

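### The trial is sized on change in Katz, but the stated analysis names no adjustment for premorbid Katz, centre or MMSE stratum; naming it costs nothing and can only help precision, by an unknown amount

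*Protocol article*

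**What the plan says.** The Primary outcome section of the protocol article defines the endpoint as Katz ADL six months after discharge, "compared to premorbid functioning two weeks prior to hospital admission". The Sample size calculation section takes the before-after difference in Katz, "divided by the SD of the difference scores of the control group", and works with an effect size of 0.25, which leads to 253 evaluable patients per arm. The Randomisation and blinding section places randomisation after the baseline assessments and says that it is "stratified by study centre and level of cognitive functioning" (MMSE 24 or above versus below 24).

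The Data analysis section then says: "The main analysis focuses on a comparison between the trial intervention and control group of the primary outcome, the Katz ADL index score". It extends the same approach to the secondary outcomes and adds Kaplan-Meier curves and a log-rank test for survival. It names no test, model or covariate for the Katz comparison and no strata for the log-rank test. It also does not say whether the quantity compared is the six-month score or the change from premorbid.

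**The concern.** Three pieces of information that may predict six-month function are in hand before allocation: premorbid Katz, centre and cognitive stratum. Katz is part of the admission assessment, and ADL functioning stays in the shortened assessment for very ill and cognitively impaired patients. The stratum has to be known in order to randomise.

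If the stated comparison is carried out as a simple contrast of change scores, premorbid Katz enters with a fixed coefficient of 1 rather than the coefficient that the data support. The strata that shaped the allocation would be left out. The result would be valid but could be less precise than the same patients allow. When the true regression slope differs from 1, a chance imbalance in premorbid Katz is also not fully removed from the particular estimate obtained.

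Precision already paid for is at stake, not the validity of the trial.

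**Working it through.** **Inputs from the documents.** Two-sided alpha 5%, power 80%, d = 0.25 in units of the SD of change, 253 evaluable per arm, 25% attrition, three centres, two MMSE strata.

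**Inputs that the documents do not give, so assumed over a range.** rho, the correlation of premorbid with six-month Katz; k, the ratio of the six-month SD to the premorbid SD; and the share of residual variance that the strata explain.

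**Step 1: the plan's own figure.** Normal approximation: n per arm = 2(1.96 + 0.84)²/0.25² = 252 after rounding up. The t-test version gives 252.13, hence 253 per arm and 506 in total. Power at 253 per arm is 80.1% (t) or 80.3% (normal). Inflation: 506/0.75 = 674.7, against 674 stated. The sizing reproduces.

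**Step 2: adjusted analysis against change score.** In units of the premorbid variance:
- change score: 1 + k² − 2·rho·k
- six-month score adjusted for premorbid: k²(1 − rho²)
- ratio, adjusted to change: k²(1 − rho²)/(1 + k² − 2·rho·k)

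The first minus the second equals (1 − rho·k)², which is never negative. So in large samples adjustment cannot lose to the change score, and the two tie when the slope rho·k equals 1.

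**Step 3: equal SDs (k = 1).** The ratio reduces to (1 + rho)/2. Power at 253 per arm is Φ(0.25·√(253/2)/√ratio − 1.96).

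| rho | variance ratio | evaluable N for 80% power | power at 253 per arm |
|---|---|---|---|
| change score | 1.00 | 504 | 80.3% |
| 0.5 | 0.75 | 378 | 90.1% |
| 0.6 | 0.80 | 402 | 88.2% |
| 0.7 | 0.85 | 428 | 86.2% |
| 0.8 | 0.90 | 454 | 84.2% |

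The equivalent saving is 504 − 378 = 126 down to 504 − 454 = 50 evaluable patients.

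**Step 4: wider spread at six months.**

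| k | rho | slope rho·k | variance ratio | power at 253 per arm |
|---|---|---|---|---|
| 1.25 | 0.7 | 0.88 | 0.98 | 81.0% |
| 1.25 | 0.8 | 1.00 | 1.00 | 80.3% |
| 1.5 | 0.6 | 0.90 | 0.99 | 80.6% |

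For example, at k = 1.25 and rho = 0.7: 1.5625 × 0.51/(2.5625 − 1.75) = 0.797/0.8125 = 0.98.

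**Step 5: the strata.** Suppose centre and MMSE stratum explain a further 1% to 5% of residual variance (k = 1). At rho 0.5 and 1%, the ratio is 0.75 × 0.99 = 0.742 and power goes from 90.1% to 90.4%. At rho 0.8 and 5%, it is 0.90 × 0.95 = 0.855 and power goes from 84.2% to 86.0%. The addition is about 0.3 to 1.8 points.

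**Step 6: if raw six-month scores were compared instead.** Keep the same absolute effect and k = 1, so that the effect in six-month SD units is 0.25·√(2(1 − rho)). Unadjusted power is then 80.3% at rho 0.5 and 58.6% at rho 0.7, against 90.1% and 86.2% with adjustment. The Data analysis section does not settle which score is meant, so naming the estimator is useful on this ground too.

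**The case against.** The strongest objection is that the article does not commit to an unadjusted analysis. A comparison between arms is compatible with a covariate-adjusted model, and a journal article commonly leaves the covariate set to the full protocol or analysis plan, neither of which is shown. This stands. A reader might infer that the plan is fixed as unadjusted, but the text supports only that it names no adjustment.

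A reader might also infer that the gain must be large. The documents do not support that, because they give neither the correlation nor either SD. A wider six-month spread is plausible: nursing-home residents are excluded at entry, and the abstract expects 30% of survivors to have declined by three months while others have not. In that case the gain may almost vanish.

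Nor does a change score over-correct whenever the correlation is below 1. The condition is a slope below 1. At k = 1.25 and rho = 0.8 the slope is exactly 1, and at k = 1.5 and rho = 0.8 it is 1.2, so the change score would under-correct. Under randomisation, chance imbalance does not bias the estimator on average, and the unadjusted standard error already allows for it.

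Finally, an unstratified log-rank test is an acceptable method.

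These points limit the size and tone of the concern. They do not remove it, because adjustment has no large-sample cost relative to the change score whatever rho and k are, and its inputs are already collected.

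**Conclusion.** The point holds as an improvement that costs nothing, not as an error. The sample size is right on its own terms, and the comparison as described would be valid.

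The large-sample gain over a change-score analysis cannot be negative, but its size cannot be fixed from the documents. It is 25% to 10% of variance (power about 90% to 84% instead of 80%) if the SDs are equal and rho lies between 0.5 and 0.8. It is about 2% to 0% if the six-month SD is 1.25 times the premorbid SD and rho is 0.7 to 0.8.

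Nearly all of any gain in power comes from premorbid Katz. The strata add little, but including them brings the standard error into line with the stratified randomisation. The adjustment does nothing about the 25% mortality expected by six months, which is a separate matter.

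**What to change.** In the Data analysis section, or in the analysis plan before unblinding if that is where the model belongs, state the primary analysis as a linear regression of six-month Katz on treatment arm, premorbid Katz, study centre and MMSE stratum (below 24 versus 24 or above). Report the adjusted mean difference with its 95% confidence interval. This also settles which Katz quantity is compared. Stratify the log-rank test by centre and MMSE stratum. If the analysis plan already says this, one sentence pointing to it is enough.

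The cost is wording only: no further data, visits or patients. The sample size need not change, and any gain is best kept as a margin because rho and k are unknown.

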**Methods/Design:**

Three hospitals in the Netherlands will participate in the multi-centre, double-blind, randomised clinical trial comparing a pro-active multi-component nurse-led transitional care program to usual care after discharge. All patients acutely admitted to the Department of Internal Medicine who are 65 years and older, hospitalised for at least 48 hours and are at risk for functional decline are invited to participate in the study. All patients will receive integrated geriatric care by a geriatric consultation team during hospital admission. Randomization, which will be stratified by study site and cognitive impairment, will be conducted during admission. The intervention group will receive the transitional care bridge program, consisting of a handover moment with a community care Care Nurse (CN) during hospital admission and five home visits after discharge. The control group will receive 'care as usual' after discharge. The main outcome is the level of ADL functioning six months after discharge compared to premorbid functioning measured with the Katz ADL index. Secondary outcomes include; survival, cognitive functioning, quality of life, and health care utilization, satisfaction of the patient and primary care giver with the transitional care bridge program. All outcomes will be measured at three, six and twelve months after discharge. Approximately 674 patients will be enrolled to either the intervention or control group.

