##### Step 1: The experimental discharge procedure including transition of care

This step concerns the transfer of care from hospital to primary care. The care during this phase and the second phase will be provided by a community care nurse (CN). The CN is a bachelor level educated nurse with a special focus on the elderly. The CN can work in a general practice, within a home care organisation or can be affiliated to a nursing home.

The transition from hospital to home consists of the following sub-steps.

(a) A handover for the care and treatment plan is made by the geriatric consultancy team and is coordinated by the CNS as part of the integrated care plan at least two days before discharge from hospital. This plan includes the ongoing interventions and recommendations for care in the primary care setting.

(b) The transition of care-plan made by the CNS will be offered to the primary care CN of the patient who is visiting the patient in hospital before discharge.

(c) After visiting patient in the hospital, the CN will discuss the care plan with the (substitute) General Practitioner (GP) of the patient.

(e) Guided by the care and treatment plan handed over from the hospital and depending on the needs of the patients and caregiver, additional support will be enabled by the CN (for example consisting of dietician, occupational therapist, the elderly welfare consultant, physiotherapist and/or pharmacist).

It is expected that approximately 6% of the patients leaving hospital are not discharged home but will be admitted in an intermediate care facility or rehabilitation care in a nursing home. In this subgroup a CN from the nursing home or rehabilitation centre will visit the patient in the hospital.

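### The predefined subgroup by discharge destination conditions on a post-randomisation event, and its nursing-home stratum has only about 15 survivors per arm

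*Protocol article*

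**What the plan says.** The Data analysis section of the protocol article names two subgroup analyses. The first is by destination: "We will perform a predefined subgroup analysis for discharge destination (patients discharged to home versus nursing home". The second is by baseline risk: "Separate subgroup analysis will also be conducted on patients at intermediate (ISAR-HP score of two or three) and high risk for functional decline".

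On timing, the abstract says: "Randomization, which will be stratified by study site and cognitive impairment, will be conducted during admission". The section Randomisation and blinding places allocation after consent and baseline assessment, stratifies by centre and by MMSE (24 or more versus below 24), and states that the hospital teams and community nurses know the allocation.

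Step 1 of the intervention takes place before the patient leaves hospital. A handover plan is prepared no later than two days ahead of discharge, and the community nurse visits the patient on the ward. The plan then goes to the GP, and extra support is organised as needed. The same section gives the expected size of the smaller stratum: "It is expected that approximately 6% of the patients leaving hospital are not discharged home". These patients go to intermediate care or to nursing-home rehabilitation.

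Two other statements bear on the point. The Participants section excludes people who came from a nursing home. The Secondary outcomes section counts institutionalization within health care utilization.

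**The concern.** A subgroup effect can be read causally when the subgroup is fixed before allocation, because randomisation then balances the arms inside each subgroup. Discharge destination is fixed afterwards. By that time the experimental arm may already have received its handover, ward visit and arranged support from unblinded staff. If the programme moves even a few frail patients from one destination to the other, the patients in a given stratum differ between arms for reasons other than the effect on ADL.

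Destination cannot be treated as a proxy for where the patient lived before, because nursing-home residents are excluded at entry. A nursing-home discharge is always a new event after admission, and it is close to something the trial sets out to measure.

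The second difficulty is size. With about 6% of patients not going home, the smaller stratum may be too thin to say anything about the programme in that setting. At stake is a result carrying the label predefined that would be read as the programme's effect in nursing-home patients, although it is neither randomised nor precise.

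**Working it through.** **Order of events**

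1. Consent and baseline assessment, then randomisation during admission (Abstract; Randomisation and blinding).
2. Experimental arm only: handover plan, ward visit by the community nurse, discussion with the GP, support arranged (Step 1).
3. Discharge to a destination.
4. Katz ADL score six months later (Primary outcome).

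The subgroup variable arises at stage 3, after the arms have begun to diverge at stage 2.

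**Inputs for the size check**

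- Effect size 0.25: "Although an effect size of 0.25 can be defined as small" (Sample size calculation). I work in units of the SD of the change score, so SD = 1.
- Two-sided alpha 5% and power 80% (same section), giving multipliers 1.96 and 0.84.
- Evaluable patients: "with a total of 506 patients (253 patients per treatment arm".
- Mortality: "To allow for attrition due to mortality, which is expected to be 25% six months after admission"; 674 to be enrolled.
- Share not going home: 6% (Step 1).

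**The plan's own figures**

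- n per arm = 2 × (1.96 + 0.84)² / 0.25², which with unrounded multipliers rounds up to 252, against 253 stated. Power with 253 per arm is 80.3%.
- 506 / 0.75 = 674.7, or 675 rounded up, against 674 stated.

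Both reproduce to within one patient.

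**Nursing-home stratum**

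- Enrolled: 674 × 0.06 = 40.4, about 20 per arm.
- Alive at six months: 40.4 × 0.75 = 30.3, or 15.2 per arm.
- Standard error of the arm difference: √(2/15.2) = 0.363 SD.
- 95% CI half-width: 1.96 × 0.363 = 0.71 SD (0.74 with the t distribution).
- Effect detectable with 80% power: 2.80 × 0.363 = 1.02 SD.
- Power for 0.25 SD: Φ(0.25/0.363 − 1.96) = Φ(−1.27), about 10%.

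**Home stratum**

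- (506 − 30.3) / 2 = 237.8 per arm.
- Power for 0.25 SD: 78%.

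**Difference in effect between the strata**

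- Standard error: √(2/15.2 + 2/237.8) = 0.374 SD.
- Detectable with 80% power: 2.80 × 0.374 = 1.05 SD, a little over four times the design effect.
- Power for a difference of 0.25 SD: about 10%.

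**Sensitivity to the 6%** (the other shares are assumptions; 25% mortality throughout)

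| Share not home | Survivors per arm | Power for 0.25 SD | 95% CI half-width |
|---|---|---|---|
| 3% | 7.6 | 7% | 1.01 SD |
| 6% | 15.2 | 10% | 0.71 SD |
| 10% | 25.3 | 14% | 0.55 SD |
| 20% | 50.6 | 24% | 0.39 SD |

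If mortality in this stratum were 40% or 50% (assumptions) with the share at 6%, about 12 or 10 per arm would remain.

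**Leverage of a shift in destination**

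One patient is 1/15.2 = 6.6% of a nursing-home stratum arm, but only 1/237.8 = 0.4% of a home stratum arm. A small shift in destination would therefore disturb the smaller stratum far more than the larger one.

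**The case against.** The strongest reply is that destination may be settled before the programme can affect it. Step 1 says that patients bound for a nursing home or rehabilitation centre are visited in hospital by a nurse from that institution, so for many of them the destination must already be expected. Both arms also receive the same geriatric assessment and care plan in hospital, so the difference before discharge is modest. This stands as a limit. A reader might infer that the programme does change destination and that the subgroup results will be biased. The article does not show this and gives no figure from which to compute it. What remains is that nothing in the design prevents such influence, and naming the analysis in advance does not restore comparability.

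A second reply is that subgroups are seldom powered, that the article claims no power here, and that the promised 95% confidence intervals would show the imprecision. This is fair as far as it goes. A reader might also infer that the whole destination analysis is unusable. That goes too far: the home stratum is nearly the whole trial, and the precision objection does not reach it.

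A third reply is that destination is of interest because delivery differs by setting, with a different nurse and a nursing home physician in place of the GP. That is a good reason to describe results by setting. It does not make the comparison a randomised one.

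Finally, a reader might take the announced separate ISAR-HP analyses to be an error too. The document does not support that. ISAR-HP is scored before randomisation, the word may simply mean additional, and whether an interaction term is fitted is a detail an article normally leaves to the full protocol or analysis plan.

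**Conclusion.** The point holds in a limited form. The destination subgroup compares the arms within strata formed after randomisation and after an unblinded intervention has begun, so those comparisons lack the protection of randomisation. The bias is a credible risk of unknown size. It applies in principle to both strata, though the home stratum is far less sensitive to a few patients changing destination.

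The precision problem is confined to the nursing-home stratum and to the contrast between strata. The figure of about 15 survivors per arm rests on three assumptions: that the 6% applies to this trial's enrolled patients, that all of them count as nursing home although the 6% also covers intermediate care, and that the overall 25% mortality holds in this group. Moving intermediate-care patients out of the stratum, or higher mortality in it, would lower the figure. The conclusion does not depend on the exact share, since power is still only 24% if 20% do not go home.

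This concerns a stated choice in the article and not a missing detail. It leaves the primary comparison and the sample size untouched. It should be corrected, but it does not threaten the trial's main result.

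**What to change.** In the Data analysis section:

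- Report discharge destination by arm as a descriptive outcome.
- If results within destination are still wanted, label them exploratory and non-causal, and say that the strata are formed after randomisation. State where patients discharged to intermediate care are counted.
- Base subgroup inference on factors fixed before randomisation and already collected: ISAR-HP 2–3 versus 4–5, and the MMSE stratification factor. For each, give the treatment-by-subgroup interaction estimate with its 95% confidence interval.

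The cost is a few lines of text and no extra data. What is lost is a nominally confirmatory nursing-home estimate, which about 15 patients per arm could not supply. The replacement has limits as well. With an even split of the 506 evaluable patients (an assumption, and the most favourable case), each cell has 126.5 patients. The interaction standard error is then √(2/126.5 + 2/126.5) = 0.178 SD, and the detectable difference is 2.80 × 0.178 = 0.50 SD. These interactions should therefore be read from their intervals, but they are valid randomised comparisons and, in that case, about twice as precise as the destination contrast.
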